## Abstract

**Background:**

Clients with severe to profound intellectual disabilities (SPID) and challenging behavior (CB) and the professional caregivers that support them are vulnerable to high stress levels, which negatively impact their well-being and the quality of care. CB is thought to result from an increase in the intensity and frequency of clients’ stress experiences. In turn, staff members experience stress in dealing with this behavior, and stressed staff members might behave in ways that increase clients’ stress levels, contributing to the origin and maintenance of CB. Research into these dyadic interactions between clients and staff is scarce for people with SPID, especially in real-life situations. The barriers of studying stress in this population include clients’ difficulties in communicating stress experiences and the lack of an objective continuous measure of stress.

**Objective:**

This paper presents a protocol for studying patterns of physiological stress in 15 client-caregiver dyads in the 30 minutes preceding incidents of CB compared to control periods without CB and the interplay between the stress levels of clients and professional caregivers.

**Methods:**

We will conduct 15 single-case studies to assess patterns of physiological stress in dyads of clients with SPID and professional caregivers prior to CB in several Dutch residential institutes. Client-caregiver dyads will wear the Empatica E4 wristband for 20 sessions of 3 to 8 hours without interruptions of daily routines while caregivers report clients’ CB. The physiological measures obtained will be electrodermal activity (microsiemens) and heart rate (beats per minute). A multilevel model with repeated measures at the incident level nested within the person level will be applied, employing separate models for electrodermal activity and heart rate to compare stress levels in the 30 minutes prior to incidents with control epochs. Covariates in the models include movement, temperature, and gender. In addition, cross-recurrence quantification analyses will be performed to study the synchronization between the stress levels of clients and professional caregivers.

**Results:**

The Ethics Committee of the Radboud University (NL-number: NL71683.091.19) approved the study on February 12, 2020. In total, 15 organizations have declared their commitment to participate in the study. The first result is expected in the spring of 2022.

**Conclusions:**

Study results will demonstrate whether changes in patterns of electrodermal activity and heart rate are apparent in the 30 minutes preceding an incident of CB compared to baseline levels when the client does not engage in CB. The synchronization between caregivers’ and clients’ physiological stress levels will be explored with cross-recurrence quantification analyses. Insights into the physiological stress levels of clients and caregivers may contribute to a reduction of CB and an improvement of both clients’ and caregivers’ safety and well-being.

**International Registered Report Identifier (IRRID):**

DERR1-10.2196/24911

## Introduction

### Background

According to the Dutch Healthcare Inspectorate, approximately 20% of the 30,000 people with intellectual disabilities (ID) living in Dutch residential institutes show severe and enduring challenging behavior (CB) [1]. CB most often includes aggression or self-injury [1] and can severely diminish clients’ quality of life [2]. The prevalence of CB increases with the severity of ID, resulting in a vulnerable group of clients with severe to profound ID (SPID) and CB [1,3]. Clients with SPID, especially in the case of CB, depend to a great extent on the support of professional caregivers in residential institutes for their physical and emotional well-being. It is well-established that CB can be stressful for caregivers, affecting caregivers’ well-being and the quality of support they provide [4]. Caregivers have reported that they are often surprised by clients’ CB and perceive the mere possibility of CB occurrence as highly stressful [5], which in turn may affect the stress experienced by clients. In addition, clients with SPID and CB perceive stress in a more frequent, intense, and sustained manner compared to the general population but lack sufficient coping skills to manage stress. Associations between stress and the origin and maintenance of CB have been reported, and CB is often a maladaptive response to stress [2]. This study addresses stress in clients with SPID and professional caregivers prior to incidents of CB.

### The Importance of Professional Caregivers’ Stress

Caregivers of clients with CB report more severe stress levels than other professionals serving clients with ID [6]. In several studies, caregivers rated clients’ CB as a highly stressful aspect of their work, and associations between the exposure to CB and caregivers’ stress have been repeatedly shown [7,8]. These associations may be moderated or mediated by caregivers’ attributions, coping styles, beliefs, self-efficacy, and training [7,8]. Specifically, Bromley and Emerson [9] reported that stress when supporting clients with CB is related to “the ‘daily grind’ of caring, their difficulty in understanding the person’s behavior, the unpredictability of the behavior, and the apparent absence of an effective way forward”. Several organizational variables (eg, workload, job variety, and support) have been identified as stressors as well [8,10]. CB and stress have a clear impact on caregivers’ psychological well-being and are associated with sickness, absenteeism, and staff turnover [10,11]. Importantly, stress impacts the quality of care [12]. The quality of care benefits from high-quality interactions between caregivers and clients [13], and inadequate caregiver-client interactions contribute to the origin and maintenance of CB [14]. Stress negatively affects the quality and quantity of these interactions and the caregiver’s ability to deal with CB effectively [4,7]. Specifically, stressed caregivers interact less often with clients, engage in more negative and less positive interactions, and are more likely to behave in ways that contribute to the origin and maintenance of CB [7,14].

### Understanding Stress in Clients With SPID and CB

CB may be a maladaptive response to perceived stress, and research has shown an association between clients’ stress and CB [2]. Janssen, Schuengel, and Stolk [2] applied an explanatory model based on theories about stress and attachment to the development of CB among clients with SPID. According to this stress-attachment model, the combination of stress and insecure attachment puts people with SPID at risk for CB. Specifically, people with SPID perceive stress in a more frequent, intense, and sustained manner when compared to the general population, but often lack appropriate coping skills to deal with stressors [2]. To deal with stressors without sufficient coping skills, people fall back on the support of an attachment figure (ie, someone to whom one is securely attached) [15]. Access to typical attachment figures (ie, parents, close friends, and mentors) is limited in residential institutes [16]. Therefore, secure attachment to professional caregivers is important for clients to receive emotional support in stressful situations. Indeed, clients who show more secure attachment behavior towards caregivers show less CB [15]. Clients who do not experience high-quality interactions with caregivers are at risk of developing insecure attachment relationships, and an accumulation of stress might cause CB [17]. Limited cognitive skills have been identified as precursors of insecure attachment, increasing the risk for CB following stress in people with SPID [2].

### Physiological Indicators of Stress

One of the difficulties in studying stress in clients with SPID and CB is the communicative shortcomings associated with clients’ ability and caregivers’ difficulties interpreting clients’ communicative signals [2]. Although caregivers try to anticipate CB by relying on the mixed and difficult-to-interpret signals from clients that might indicate stress, caregivers lack insight into clients’ stress experiences and report being surprised by CB [5]. Further, most research on caregiver stress relies on a range of questionnaires, measuring subjective experiences with variations based on, for example, caregivers’ age and experiences. The results from these studies are hard to interpret due to methodological differences in measuring stress and the lack of an objective, continuous measure of stress [10]. Since psychologically stressful events change people’s physiology, studying physiological stress increases insight into patterns of stress that precede incidents of CB [2]. In addition, physiological measures of caregiver stress are significantly associated with burnout symptoms over time [11]. Both physical and emotional stress result in physiological responses characterized by the dual innervation of the autonomous nervous system [18]. During stressful events, increased activity of the sympathetic nervous system and decreased parasympathetic nervous system activity is typically observed, resulting in increased heart rate, electrodermal activity, and blood pressure [19]. However, more complex relations between the innervation of both branches and aggression have been observed as well [20]. Although physiological measures of stress have been studied repeatedly, most studies are conducted in experimental settings. The development of wearable wireless devices has increased the possibilities of measuring physiological indicators of stress nonintrusively and continuously in real-life settings [5]. Electrodermal activity (EDA) and heart rate (HR) are reliable physiological measures of stress that can be monitored with these wearables [21]. Some naturalistic studies have been performed to assess physiological stress using wearables in real-life settings. Rises in EDA [22-24] and HR [22] have been reported in the 30 minutes prior to aggression in psychiatric patients. Physiological stress and motion measures can be used to predict aggression to others in the upcoming minutes in people with autism spectrum disorder (ASD) [25]. In an earlier study, Noordzij, Scholten, and Laroy-Noordzij [5] have shown the possibilities of measuring EDA and HR in clients with SPID and the caregivers that support them during incidents of CB. In inpatient forensic mental health services, caregivers reflected on the utility of technological devices to provide early warnings for impending aggression [26].

### Our Study

The literature has shown the predictive value of physiological measures of stress for upcoming aggression in psychiatric patients and people with ASD. Although the possibilities of using wearables to study physiological stress in clients with SPID and CB have been shown, not much is known about patterns of physiological stress prior to CB in clients with SPID or in the caregivers that support them. Since the existing literature shows the well-being of caregivers is affected by stressors associated with clients’ CB, and the relationship with caregivers is important for clients to cope with stress and prevent CB, studying the reciprocity between clients’ and caregivers’ physiological stress is an eminent step in further increasing insights into patterns of stress and the origin of CB. Therefore, we hypothesize a reciprocal model in this study of stress and CB (Figure 1). The model suggests that: (1) client stress is associated with CB [2,15,17], (2) caregiver stress contributes to CB [4,7,14], (3) CB contributes to caregiver stress [6-9], and (4) caregiver stress impacts client stress and vice versa.

**Figure 1 figure1:**
[figure not shown]
A reciprocal model of stress and challenging behavior in caregivers and people with severe to profound intellectual disability.

This naturalistic study explores patterns of physiological stress (ie, EDA and HR) in clients with SPID and professional caregivers prior to CB in Dutch residential institutes and the synchronization between client and caregiver patterns of stress. We address the following research questions:

Do patterns of physiological stress in clients with SPID and professional caregivers in the 30 minutes preceding an incident of CB differ from control periods of 30 minutes without CB?Do the physiological stress levels of caregivers impact clients’ physiological stress levels and vice versa?

We hypothesize that a significant rise in EDA and HR is apparent in both clients and caregivers in the 30 minutes preceding an incident of CB compared to baseline levels when the client does not engage in CB. In addition, we hypothesize physiological synchrony—a mutual change in autonomic nervous system activity—between caregivers and people with SPID and CB. Physiological synchrony has been shown in some interaction partners, including parent-infant dyads [27,28], strangers [29], and romantic couples [30]. However, to our knowledge, physiological synchronization has not been studied before in dyads of professional caregivers and clients with SPID and CB.

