### Study Procedure

Clients and caregivers will wear the wearable during 20 sessions of 3 to 8 hours. The sessions do not interfere with daily routines and activities. The caregiver will attach the wearable to their own and their client’s wrist. Caregivers will follow a protocol developed specifically for clients with SPID and CB to attach the wearable to the client’s wrist because the attachment of the wearable may induce stress for both caregivers and clients due to the deviation from the daily routine [5] (see Multimedia Appendix 1). The protocol is personalized per dyad. To minimize the influence of the wearable on stress and behavior, clients and caregivers will wear the wearable prior to the study to familiarize themselves with it. When the wearable no longer induces stress to the client and the caregiver, we will start collecting measurements. The data are saved in the memory of the device and exported into a secured server via USB.

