### Statistical Analyses

Descriptive statistics regarding incidents of CB and stress levels will be described in relation to demographic data. As measuring physiological stress in real-life situations results in artifacts (ie, disturbances in the signal due to excessive movements), the data will be visually inspected, and impossible values removed. Subsequently, data will be corrected automatically with a proven method described by Taylor and colleagues [40]. Statistical analyses will be performed in R-4.0.4.

EDA and HR of clients and caregivers in the 30 minutes prior to an incident of CB will be compared with 30 minutes of control periods in which the client did not engage in CB. A multilevel model with repeated measures (level 1) at the incident level (level 2) nested within the person level (level 3) will be used. For the repeated measures (level 1), the 30-minute sessions are divided into epochs of 5 minutes. Separate models for PPM, SCL, and HR will be considered. Covariates in the models include movement, temperature, and gender.

Recurrence Plots (RPs) of the 30 minutes prior to an incident of CB will be made. Cross-Recurrence Quantification Analysis (CRQA) will be performed to determine if patterns of stress in the time series of caregivers are recurring in the time series of clients, and vice versa, in a moment prior, simultaneously, or later in the time series [41]. The Recurrence Rate (RR), a ratio of the number of recurrent points over the total possible number of recurrent points, will be calculated. The RR indicates how often a point in one time series recurs in another time series. Determinism, which is the number of recurrent points that form a diagonal line in an RP relative to the total number of recurrent points, will be calculated. Determinism represents the recurrence of patterns over time, and a high determinism indicates the synchronization of patterns of physiological stress between the caregiver and the client. A diagonal Cross-Recurrence Profile provides insights into who is leading in the pattern of physiological stress prior to an incident. In other words, is the recurring pattern of stress first noticeable in a client and subsequently in the caregiver, or vice versa? CRQA is performed using the R package “crqa” [41].

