## Discussion

### Conclusions

This protocol study describes a series of single-case studies assessing stress patterns in professional caregivers and clients with SPID prior to incidents of CB in Dutch residential institutes and the synchronization or desynchronization between these patterns. We hypothesize that a significant rise in EDA and HR is apparent in clients and caregivers in the 30 minutes preceding an incident of CB compared to control periods without CB. In addition, we expect a reciprocal influence of caregivers’ and clients’ stress levels, meaning an increase in caregiver stress is followed by the rise in client stress and vice versa.

One of the study's strengths is that stress is measured in a real-life setting without interfering with daily routines. While measuring physiological stress in real-life settings results in artifacts, the models in this study will be corrected for movement and temperature. A visual and an automatic correction of artifacts will be performed as well [40]. In an earlier study [22], a considerable number of artifacts, besides movement and temperature, were found in the data related to the tightness of the wearable on the wrist, which will be addressed when instructing participants. Besides movement and temperature, gender is included as a covariate in the models. Meta-analyses have shown that the associations between physiological measurements and behavior are similar for men and women, but the strength of the associations varies [42-44].

Another strength of this study is that interpersonal variations are accounted for by comparing stress of the same subject in periods prior to CB with control periods without CB. This comparison is important as people have different baseline values of EDA and HR [22]. In addition, the stress of both client and caregiver is assessed in the same time frame. This enables us to study the reciprocity between client and caregivers’ stress, which is important as client-caregiver interactions impact the development of stress and CB and are vital to the quality of support caregivers can provide [2,13].

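### The pre-incident contrast has no session term, so a session-wide elevation on days with challenging behavior can be read as a rise in the preceding 30 minutes

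*Protocol article*

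**What the plan says.** The first research question (Introduction, Our Study) is whether stress patterns "in the 30 minutes preceding an incident of CB differ from control periods of 30 minutes without CB". The hypothesis in the same section is a significant rise in both members of the dyad "compared to baseline levels when the client does not engage in CB". The Abstract (Methods) states the contrast on levels: the models are used "to compare stress levels in the 30 minutes prior to incidents with control epochs".

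Methods, Statistical Analyses, repeats that the pre-incident data "will be compared with 30 minutes of control periods in which the client did not engage in CB" and fixes the hierarchy: "A multilevel model with repeated measures (level 1) at the incident level (level 2) nested within the person level (level 3) will be used". The listed covariates are movement, temperature and gender.

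Methods, Study Procedure, sets up the data: "Clients and caregivers will wear the wearable during 20 sessions of 3 to 8 hours". Eligibility requires CB several times a week, which does not imply CB in every session. The Discussion presents the comparison within the same subject as a strength, because baseline values differ between people. No section names session or day as a matching factor, a model level or a covariate.

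**The concern.** Grouping by person removes a person's overall level. It does not remove the level of a particular session. The two kinds of window are also drawn from sessions in different ways: a pre-incident window needs a session with CB, while a control window, as defined, can come from any session.

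If sessions with higher arousal throughout are also the sessions with more CB, pre-incident windows over-represent high sessions. The estimated difference then contains a session effect that was present hours before the incident.

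This matters because of the conclusion to be drawn. The Abstract says the results will show whether changes are apparent in the 30 minutes before CB, and Implications for Practice looks ahead to informing caregivers so that they can anticipate CB. A worse day and an imminent incident are different messages, and the planned estimate cannot tell them apart.

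**Working it through.** **Inputs from the article.** There are 15 dyads with 20 sessions each of 3 to 8 hours, which is 6 to 16 half-hour windows per session and 120 to 320 per person. The contrast is on levels, the model levels are epoch, incident and person, and the covariates are movement, temperature and gender. The article gives no session variance, no CB rate per session and no power calculation, so there is no figure of its own to reproduce.

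**Assumptions.** The session standard deviation, the strength of the link between session arousal and CB, and about 100 to 120 incidents in total are all assumed. Each window is represented by its mean.

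**Step 1, algebra.** Write a window mean as person + σ·u + δ·(pre-incident) + noise, where u is the standardized session offset, σ its standard deviation and δ the true rise. With person effects removed, the expected difference is

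δ + σ·(mean u in pre-incident windows − mean u in control windows).

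If the CB rate is proportional to exp(β·u) and u is normal, the mean of u in pre-incident windows is β. With controls from any session the second mean is about 0, so the spurious part is about β·σ. With controls from the same session it is 0.

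**Step 2, size in units of the within-session window SD.** The odds of CB rise 1.25, 1.5 or 2 times per SD of session arousal, so β = ln 1.25 = 0.22, ln 1.5 = 0.41 or ln 2 = 0.69.

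| Session SD | β·σ at 1.25 / 1.5 / 2 | False positives, any-session controls |
|---|---|---|
| 0.5 | 0.11 / 0.20 / 0.35 | 15% / 41% / 86% |
| 1 | 0.22 / 0.41 / 0.69 | 31% / 80% / about 100% |

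The last column is from simulation (800 runs per setting, δ = 0, nominal 5%, person effects only). The simulated spurious difference ran from 0.10 to 0.65, close to the algebra. The within-session contrast had bias near 0 and rejected in 4-6% of runs. A separately written simulation over the same ranges gave 10-89% at session SD 0.5 and 38-100% at SD 1, against 4-5% within session.

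**Step 3, milder settings.** Here the unit is the total within-person SD, with one control per incident, a mean of 0.4 incidents per session (0.4 × 20 × 15 = 120) capped at 3, δ = 0 and 500 runs. Each cell lists session shares of variance of 0.1 / 0.3 / 0.5.

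| Controls from | β | Spurious rise (SD) | False positives |
|---|---|---|---|
| Any session | 0.25 | 0.07 / 0.13 / 0.16 | 10% / 17% / 25% |
| Any session | 0.5 | 0.15 / 0.26 / 0.33 | 20% / 50% / 72% |
| CB-free sessions only | 0.25 | 0.10 / 0.18 / 0.24 | 12% / 31% / 46% |
| CB-free sessions only | 0.5 | 0.21 / 0.37 / 0.47 | 39% / 80% / 94% |
| Same session, session effects | 0 to 0.5 | −0.01 to +0.01 | 3.0-6.8% |

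The algebra agrees: at β = 0.5 and share 0.5, 0.5 × √0.5 = 0.35 against 0.33 simulated. The simulation error of a 5% rate in 500 runs is √(0.05 × 0.95 / 500), about 1 percentage point, so 3.0-6.8% is compatible with nominal.

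**Step 4, session differences unrelated to CB (β = 0).** Mean bias is about 0. False positives are 4-6% with any-session controls and 6-10% with controls from CB-free sessions only.

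**Step 5, a check on the remedy.** Same-session controls can include recovery after an incident. With a true rise of 0.4 SD, post-incident windows raised by 0.4, 0.4 and 0.2 SD, session SD 0.5 and no link between day and CB, the session-effect estimate fell to 0.31, while the person-effect estimate was 0.39. With stronger recovery and build-up in the preceding half hour it fell to 0.21 against 0.40. In a further run with post-incident carry-over it fell to about 0.28, and dropping the post-incident windows restored 0.40.

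**The case against.** **The source of the controls is left open.** A reader might infer that the study takes controls from other days. The article does not say so, and a fuller protocol could require same-session controls. The level-2 wording could even mean that each incident carries its own control epochs; if those came from the same session, the problem would largely disappear. This stands as a limit on the claim. But the article does state a model and covariates, and neither contains session, while the only matching it claims is within subject.

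**The theory section does not supply the link.** It is tempting to read the statement that "an accumulation of stress might cause CB" as the study's own evidence that whole days are raised. It is not. That sentence concerns insecure attachment and poor interactions, and the nearby description of stress as sustained compares clients with the general population. Neither mentions days or sessions, so the link is an assumption, though a plausible one.

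**Band fit is not a second cause of bias.** The Discussion reports that in an earlier study "a considerable number of artifacts, besides movement and temperature, were found in the data related to the tightness of the wearable on the wrist". A reader might infer an upward bias from refitting the band each session. Nothing ties fit to days with CB, and without that tie it mainly adds noise (Step 4). Habituation over the sessions likewise needs an unsupported decline in CB, and recording starts only once the wearable no longer causes stress.

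**A time course within the window would be immune.** A constant session offset cancels from a slope over the 5-minute epochs. That is correct, but the article states a comparison of levels and commits to no slope test.

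**Higher stress on CB days may be part of the question.** The wording about baseline levels allows this, and the study is exploratory with a disclosed limit on context. That is a reason to report the between-session difference. It is not a reason to label it a rise in the 30 minutes before CB.

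**Conclusion.** The point holds in a conditional form. As stated, the contrast and model separate persons but not sessions. If sessions with higher overall arousal have more CB, and controls are not confined to the incident's session, the pre-incident difference is biased upward. The direction follows from that link. The size does not follow from the article: about 0.1 to 0.65 SD and false-positive rates from about 10% to nearly 100% illustrate the assumed ranges and do not predict this study's results.

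The documents do not support saying that the study will use controls from other days, that its theory asserts day-long elevation, or that a significant result would be false.

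**What to change.** Add session as a level between incident and person, and split the pre-incident indicator into a within-session part (centred on its session mean, or with session fixed effects) and a between-session part. A random session intercept alone is not enough, because a single uncentred coefficient still mixes the two contrasts.

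Base any statement about a rise in the 30 minutes preceding CB on the within-session estimate. Report sessions with versus without CB as a separate line. State the control-window rule, exclude windows within a stated period after an incident, and vary that period in a sensitivity analysis. Otherwise carry-over, or build-up lasting longer than 30 minutes, would pull the within-session estimate toward zero.

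The cost is in the analysis only: incident date and time are already recorded, and no new data are needed. Short sessions with CB will offer fewer eligible control windows, and CB-free sessions will inform only the between-session estimate. Precision need not suffer: with no link between day and CB and before any exclusions, the simulated standard error was 0.107 within session against 0.143 at session SD 1 (1 − (0.107/0.143)² = 44% less variance), and 0.108 against 0.115 at SD 0.5 (12% less).
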